
## 3 Methods and analysis

### 3.1 Ethics oversight

This study has been approved by the UHT Research Ethics Board (Approval No.: 21-152) and will be conducted in compliance with the principles of the Tri-Council Policy Statement: Ethical Conduct for Research Involving Humans (TCPS 2) (Canadian Institutes of Health Research, Natural Sciences and Engineering Research Council of Canada, and Social Sciences and Humanities Research Council, 2018) and International Council for Harmonization Good Clinical Practice E6 (ICH GCP E6) (Vijayananthan and Nawawi, 2008). The trial has been registered on ClinicalTrials.gov (NCT05295888).

### 3.2 Participant selection and recruitment

The trial will enroll individuals with moderate-to-severe MDD in a MDE. Treatment resistance is not a criterion for inclusion. Participants, if receiving any treatment, must remain on a stable dosage of any concomitant medications and shall have no changes to their treatment regimen 4 weeks before enrollment and during the trial. The protocol prohibits certain medications that may interfere with the effect of NIBS therapies, such as barbiturates, benzodiazepines, and certain anticonvulsants (Kaster et al., 2020). The key eligibility criteria are displayed in Table 1, and the full list is available in Supplementary Table S1.

**TABLE 1 T1:** Summary of eligibility criteria for the clinical trial examining transcranial temporal interference stimulation in major depressive disorder.

**Inclusion criteria**
(1) Male or female, 18–65 years of age (inclusive)
(2) Meet the DSM-5 criteria for MDD with a current MDE without psychotic features, as confirmed by the MINI
(3) MADRS total score of ≥20 (moderate-to-severe MDD)
(4) No change in treatment regimen in the 4 weeks prior to screening
**Exclusion criteria**
(1) Any psychiatric disorder, including substance use disorder, other than MDD or comorbid anxiety disorder due to its high co-occurrence with MDD
(2) Any neurological disorder, serious medical illness, sensory abnormality, or unstable clinical finding
(3) Active suicidal intent, confirmed by the MINI Module B (Suicidality) or MADRS item #10 score ≥4
(4) Take medications prohibited by the protocol that may interfere with the effect of tTIS
(5) Pregnant or lactating
(6) An intracranial implant (e.g., aneurysm clips, shunts, stimulators, cochlear implants, or electrodes) or any other metal object within or near the head, excluding the mouth, that cannot be safely removed
(7) Change in medication or psychotherapy treatment regimen before screening
(8) Contraindications for receiving tTIS or undergoing a magnetic resonance imaging scan

DSM 5, Diagnostic and Statistical Manual of Mental Disorders, 5th edition; MADRS, Montgomery-Åsberg Depression Rating Scale; MDD, major depressive disorder; MDE, major depressive episode; MINI, Mini International Neuropsychiatric Interview; tTIS, transcranial temporal interference stimulation.

### 3.3 Study design

This study is a pilot single-site randomized sham-controlled interventional clinical trial based at the Interventional Psychiatry Program, St. Michael’s Hospital – Unity Health Toronto (UHT) in Toronto, ON, Canada. The trial will compare a course of 10 sessions of 130 Hz tTIS stimulation vs. 10 sessions of sham stimulation, delivered over 2 weeks (Figure 1). Thirty participants with MDD will be recruited into the trial and randomized into two parallel arms (active tTIS vs. sham) in a 1:1 fashion. Block randomization will be stratified by sex to allocate participants using a secure randomization module on Research Electronic Data Capture (REDCap) (Harris et al., 2009), as sex differences in brain volume and skull anatomy influence NIBS treatment outcomes (Hanlon and McCalley, 2022). Participants, investigators, outcome assessors, and data analysis will be blinded to treatment allocation. A randomization table will be generated using an external tool and uploaded to REDCap. Once a new participant is ready to be randomized, a research coordinator external to the study will enter their sex (a stratification variable) into REDCap, and the system will use the pre-defined randomization table to assign them to a treatment group.

**FIGURE 1 F1:**
[figure not shown]
Study design of a pilot randomized sham-controlled interventional clinical trial examining the target engagement and therapeutic potential of transcranial temporal interference stimulation (tTIS) in major depressive disorder (MDD). The trial will enroll 30 participants with MDD, who will be randomized to receive active tTIS or sham stimulation in 1:1 allocation. Participants will complete 10 sessions of tTIS or sham stimulation over 2 weeks. A comprehensive clinical assessment with a semi-structured interview will take place on treatment days 5 and 10 after the stimulation (red circles). After randomized treatment, participants will undergo a post-stimulation visit and a delayed follow-up visit (green circles) scheduled 5 and 20 days after the last treatment day 10, respectively.

### 3.4 Sample size considerations

Based on studies in TES with fMRI, block design, and use of computational iterative neurostimulation (Ghobadi-Azbari et al., 2021), we expect that 30 participants will have adequate power to demonstrate target engagement of the sgACC. The proposed sample size (*n* = 30) is also based on the overall goal of (a) reasonably assessing the feasibility outcomes and (b) estimating the variability of the clinical outcome measures and is consistent with published recommendations for pilot trials designed to estimate standard deviations for larger future randomized controlled trials when the effect size is small-to-medium (Lancaster et al., 2004; Whitehead et al., 2016). As such, based on sample sizes used in pivotal TES studies (Berlim et al., 2013), we expect that 30 participants will be adequate to demonstrate the feasibility, tolerability, safety, and therapeutic effect of tTIS. Moreover, the pilot study will provide effect size estimates to design a definitive efficacy trial.

For this pilot study, to have a 90% power (i.e., being 90% confident that the effect is true and that it is not a type I/II error), the top end of the two-sided 95% confidence intervals will be the maximum confidence of having a true difference between active tTIS and sham arms. If there is no difference between active tTIS and sham arms, then *p* ≥ 0.051 will indicate no difference with a 90% confidence, and if there is a difference, then *p* ≤ 0.05 will indicate the difference with a 90% confidence. To have the medium effect size of *f* = 0.25 for the mixed-model analysis of variance (Cohen, 2013), 30 patients (15 per group) are required to have a 90% power. We anticipate having a 15% dropout rate in the randomized phase of the study due to side effects or lack of adherence to protocol and approximately a 50% response rate in the acute phase of treatment. A sample size of 15 per group will give us precise estimates of variability in the clinical outcome, namely a change in the Hamilton Depression Rating Scale 17-Item (HAM-D-17) (Hamilton, 1960) score over time (Korn et al., 2012; Cohen, 2013), and this sample size is within the recommended total sample sizes for a precise estimate of the standard deviation and correlation for HAM-D-17 scores to use in the future sample size calculation for a definitive larger scale trial (between *n* = 24 and 50) (Julious, 2005; Sim and Lewis, 2012; Billingham et al., 2013).

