#### 3.12.2 Secondary outcomes: clinical assessments

Improvement in depressive symptoms will be the main secondary outcome measure. Additional secondary outcome measures will include feasibility, safety, and tolerability metrics of rates of recruitment, withdrawals, and adherence, as well as the number and nature of AEs and serious AEs.

For continuous outcome measures, a mixed-effects model will be used to assess differences in the rate of improvement over time and the final outcome across groups. Treatment group, time, and treatment group × time interaction will be used as explanatory variables, with participant as a random factor. The significance of the treatment group × time interaction effect will be used to test the null hypothesis. For categorical outcome measures, response will be defined as a ≥50% reduction in HAM-D-17 and QIDS-SR-16 total scores at Visit 10. Remission will be defined as a HAM-D-17 total score of <8 at Visit 10. The two-tailed Chi-squared test will be used to assess the significance of any observed differences in the proportion of responders and remitters between groups.

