## 4 Discussion

The therapeutic effectiveness of NIBS in MDD has been validated across numerous studies, but, with few exceptions (Cole et al., 2020, 2022), its efficacy remains limited due to its dependence on the selection and accuracy of stimulation targets (McLoughlin et al., 2007; Herbsman et al., 2009; Fox et al., 2012; Berlim et al., 2013; Lefaucheur et al., 2017; Liu et al., 2017). Guiding NIBS with cutting-edge imaging techniques is fundamental for locating specific functional brain networks and accurately positioning stimulation sites to fit individual anatomical variations (Mir-Moghtadaei et al., 2015; Luber et al., 2017). To develop NIBS as an individualized treatment for individuals with MDD, determining a combination of suitable imaging methods is crucial for providing optimal antidepressant effects. Our clinical trial is a multi-modal neuroimaging study, where target engagement of the sgACC will be assessed across different modalities and metrics, spanning both structure and function. These data will guide the investigation of the target engagement capabilities of tTIS as a new, emerging technology that can potentially be enabled for personalized and precision psychiatry in the future.

The preliminary studies establishing its safety and effectiveness in healthy humans, as well as its unique spatial accuracy, make tTIS a desirable candidate for NIBS therapy in MDD (Wessel et al., 2021; Ma et al., 2022; Piao et al., 2022; von Conta et al., 2022; Zhang et al., 2022; Zhu et al., 2022). The present study will be the first to demonstrate target engagement of the sgACC and the therapeutic potential of repetitive tTIS in MDD. Data from this trial will provide much-needed safety and effectiveness evidence to the limited literature regarding tTIS for deep brain regions in humans. If successful, our approach of noninvasively targeting sgACC may also be translated to other psychiatric disorders of disrupted brain connectivity characterized by sgACC dysregulation and FC disturbances.

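### Section 3.4 says 30 participants are adequate to demonstrate safety, but only 15 receive active tTIS, and even an event-free result would leave serious-event rates up to about 18–22% open

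*Protocol article*

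**What the plan says.** The sample size section (3.4) states that "we expect that 30 participants will be adequate to demonstrate the feasibility, tolerability, safety, and therapeutic effect of tTIS". The reason given is that this is "based on sample sizes used in pivotal TES studies". The section gives no event rate to be detected, no rate to be ruled out and no precision target for safety.

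The design section (3.3) fixes the split: "Thirty participants with MDD will be recruited into the trial and randomized into two parallel arms (active tTIS vs. sham) in a 1:1 fashion". Section 3.6 describes the sham as a ramp-up followed at once by a ramp-down to 0 mA. The design figure legend and the study procedures show treatment followed by two follow-up visits, and describe no phase in which sham participants later receive active stimulation.

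Safety is read out in section 3.12.2 among the additional secondary outcomes, "as well as the number and nature of AEs and serious AEs". The Discussion says: "Data from this trial will provide much-needed safety and effectiveness evidence to the limited literature regarding tTIS for deep brain regions in humans".

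**The concern.** The adequacy statement speaks of 30 participants, but what they can show about the safety of active stimulation comes from the 15 who receive it. The sham arm gives a background rate for comparison and adds no exposure to the sustained current. Fifteen people can show which effects are common. They say little about serious or uncommon harms, and a small trial in which nothing serious happens is easy to over-read.

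The statement stands in the sample size justification, the natural place to look for what the trial can and cannot establish. As worded, it would permit an event-free pilot to be cited as having shown safety, when the data would still be compatible with a serious-event rate close to one in five.

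**Working it through.** **Is there a safety figure to reproduce?** No. The only calculated basis for the sample size is the efficacy statement: an effect size of "0.25 for the mixed-model analysis of variance", for which "30 patients (15 per group) are required to have a 90% power". That concerns a difference between groups in a continuous outcome. It says nothing about how well an event rate is estimated, so it cannot support the safety claim.

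**Inputs**
- Participants exposed to active tTIS: n = 15 (sections 3.3 and 3.4).
- Confidence level: section 3.4 refers to "the top end of the two-sided 95% confidence intervals", so 95% two-sided is the plan's own convention. The one-sided limit is shown as well because with zero events only the upper end matters.
- Observed serious events: 0. This is an assumption and the most favourable case, since the article states no expected or acceptable rate.

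**Upper limit after 0 events in n participants (exact binomial)**
- One-sided: 1 − 0.05^(1/15) = 0.181, or 18.1%.
- Two-sided: 1 − 0.025^(1/15) = 0.218, or 21.8%.
- Rule of three: 3/15 = 20.0%.
- Wilson: 1.96² / (15 + 1.96²) = 3.84 / 18.84 = 20.4%.

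Every method gives a limit near one in five.

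**Chance that no event is seen among 15, by true rate p: (1 − p)^15**

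| True rate | Chance of seeing none |
|---|---|
| 1% | 0.99^15 = 86% |
| 5% | 0.95^15 = 46% |
| 10% | 0.90^15 = 21% |

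**Event-free active participants needed to put the upper limit at or below a given rate: ln(0.05)/ln(1 − p) one-sided, ln(0.025)/ln(1 − p) two-sided, rounded up**

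| Rate to exclude | One-sided | Two-sided |
|---|---|---|
| 10% | 29 | 36 |
| 5% | 59 | 72 |
| 1% | 299 | 368 |

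**If all 30 were counted as exposed**, which the sham does not allow, the limit would be 1 − 0.05^(1/30) = 9.5% one-sided or 1 − 0.025^(1/30) = 11.6% two-sided. Even that would leave uncommon serious harms open.

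**The case against.** The strongest reply is that this is one loose word in a pilot protocol. The sentence is an expectation. The article sets no safety hypothesis, threshold or decision rule, and section 3.12.2 already treats safety descriptively. The abstract promises feasibility and tolerability estimates for a larger trial, and section 3.4 itself gives assessing feasibility and estimating variability as the goals of the sample size. A wide zero-event limit is normal with 15 per arm. A safety board and rules for ending stimulation and participation are in place.

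Most of this stands. The sample size is not at fault, and common tolerability events can be described with 15 people. What remains is that section 3.4 makes an explicit adequacy claim for safety that the design cannot meet, and that the claim goes further than the rest of the article.

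A reader might infer more than the text supports:
- *That the plan will declare safety shown if no serious event occurs.* No rule says so. The Discussion sentence on safety evidence promises only a contribution to a limited literature.
- *That home use is to rest on this trial's event count.* The Discussion bases it on simple electronics, low device risk and scalability, and calls the study a first step.
- *That the limit should be computed on about 13 people after the anticipated 15% dropout.* Participants who leave after being stimulated remain exposed, and some may leave because of side effects, so 15 is the right denominator.
- *That this trial is the only source on repeated tTIS in patients.* The Discussion says only that the human studies it cites were single-session and in healthy people. Those do not settle a 10-session course in depression, but the article does not claim that no other data exist.
- *That no later trial would accept such a rate.* The article states no acceptable rate.

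Counting the 15 × 10 = 150 active sessions gives a per-session limit near 3/150 = 2%, but sessions within a person are not independent, so this cannot replace the per-participant figure.

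**Conclusion.** The point holds as a correction to a stated claim. Thirty participants, 15 of them exposed, are not adequate to demonstrate safety with respect to serious or uncommon harms. At best the trial excludes per-participant serious-event rates above about 18% (one-sided) or 22% (two-sided), and it has a 46% chance of showing no case of a harm that affects one person in twenty.

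These figures assume that all 15 allocated to active tTIS receive at least one session, that no serious event is seen, and that participants are independent. One or more observed events would raise the limits. The conclusion does not depend on the choice of interval method. Enrolment, conduct and the primary analysis are unaffected. Per-arm event tables and the definition of the safety population belong in an analysis plan that is not shown, and their absence from the article is not part of this point.

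**What to change.** In section 3.4, remove safety from the list of what 30 participants are adequate to demonstrate, and add wording such as:

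> The trial will describe the safety and tolerability of tTIS and provide preliminary estimates. Fifteen participants will be exposed to active stimulation. If none has a serious adverse event, the upper 95% confidence limit for the per-participant rate will be about 18% (one-sided exact) or 22% (two-sided exact); lower rates cannot be excluded.

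The cost is a less favourable safety statement. No extra patients, visits or procedures are needed.

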Recently, several other NIBS techniques have received increased attention in depression research, as they may overcome the aforementioned limitations of ECT and DBS while achieving comparable therapeutic effects. Some notable examples include transcranial electrical stimulation (TES) and transcranial magnetic stimulation (TMS), the latter of which is FDA-approved for the treatment of TRD. Through the modulation of neuroplasticity, these NIBS modalities induce long-lasting changes in the excitability of brain regions involved in regulating thoughts, emotions, and behavior (Boes et al., 2018; Polanía et al., 2018). The therapeutic potential of NIBS stems from its ability to evoke immediate and sustained directional modulation of neural network activity in either an excitatory or inhibitory fashion (Miniussi et al., 2013; Cantone et al., 2017) or by modifying the threshold of synaptic plasticity (Karabanov et al., 2015; Hassanzahraee et al., 2018). Several meta-analyses and systematic reviews have demonstrated the efficacy and tolerability of both TES and TMS for the treatment of depression (Berlim et al., 2014; Kedzior et al., 2014; Dunlop et al., 2017; Pacheco et al., 2021). Furthermore, response and remission rates for these modalities remain in the range of 33%–45% and 16%–22%, respectively (Cao et al., 2018; Razza et al., 2020), although individual studies have shown much higher remission rates, such as with transcranial alternating current stimulation (tACS) in MDD (54% remission) (Wang et al., 2022) or the Stanford Accelerated Intelligent Neuromodulation Therapy (SAINT) protocol for neuronavigated intermittent theta-burst repetitive TMS in TRD (57%–86% remission) (Cole et al., 2020, 2022).

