Our primary aim is to demonstrate target engagement of the sgACC with tTIS in participants with MDD using the resting-state fMRI, arterial spin labeling (ASL), and diffusion-weighted MRI, as evidenced by pre- vs. post-treatment changes in its intrinsic activity, functional connectivity (FC), perfusion, and anatomical connectivity with other brain regions. We hypothesize that in participants with MDD, a course of 10-day active 130 Hz tTIS will induce engagement of the sgACC post-treatment, which will be superior to sham. Target engagement will be measured as pre- vs. post-treatment change in: (a) resting-state blood-oxygen-level-dependant (BOLD) activity, quantified by power in the BOLD characteristic frequency range (0.015–0.08 Hz), (b) perfusion metrics of cerebral blood flow (CBF), and (c) BOLD activity and CBF in resting-state functional and anatomical networks, or brain regions that are strongly coherent with the sgACC functionally and connected anatomically. We hypothesize that we will observe (a) an increase in BOLD activity in sgACC voxels in tTIS arms but not the sham due to the direct stimulation of the area, (b) an increase in CBF in sgACC voxels in tTIS arm but not the sham due to the direction stimulation of the area, (c) an increase in FC between sgACC and dorsolateral prefrontal cortex (dlPFC), ventromedial prefrontal cortex (vmPFC), and insula – the nodes that display reduced baseline resting-state FC in unmedicated MDD patients compared to healthy controls (Murrough et al., 2016; Wang et al., 2018; Cheng et al., 2021), (d) a significant association between changes in the FC of the sgACC with the abovementioned nodes and anatomical connectivity. Our secondary aim is to demonstrate, using a randomized sham-controlled design, the feasibility, tolerability, and therapeutic potential of repetitive tTIS in participants with MDD. We hypothesize that a 10-day active 130 Hz tTIS will produce significantly greater improvement than sham stimulation in scores of standardized clinical measures of mood symptoms severity in MDD, anxiety, quality of life, and functional impairment. We will also perform exploratory analyses of (a) pre- vs. post-stimulation changes in whole-brain resting-state FC of the sgACC, (b) pre- vs. post-stimulation changes in resting-state electroencephalography (EEG) spectral power after a single session of tTIS and over the course of 10 sessions, (c) pre- vs. post-stimulation changes in the amplitude and latency of the auditory mismatch negativity (MMN) event-related potentials (N1 and P1) after a single session of tTIS and over the course of 10 sessions, (d) feasibility of performing concurrent EEG acquisition during tTIS (termed tTIS-EEG), and (e) source signal propagation during concurrent tTIS-EEG using our proposed configuration for the stimulation of the sgACC with tTIS.

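### The sample-size section's adequacy claim and its reading of p ≥ 0.051 as no difference are not supported for the chi-squared tests of response and remission

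*Protocol article*

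**What the plan says.** Section 3.4 makes three statements that bear on the clinical outcomes.

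- Citing the sizes of earlier TES studies, it says "we expect that 30 participants will be adequate to demonstrate the feasibility, tolerability, safety, and therapeutic effect of tTIS".
- It describes power through "the top end of the two-sided 95% confidence intervals". It adds that, if the arms do not differ, p of 0.051 or more will show this with 90% confidence.
- It gives one power calculation, for a medium effect of f = "0.25 for the mixed-model analysis of variance", under which "30 patients (15 per group) are required to have a 90% power".

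The same section expects 15% dropout and "approximately a 50% response rate in the acute phase of treatment". It does not say which arm the 50% refers to. It gives no sham response rate and no remission rate for this trial.

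Section 3.12.2 tests continuous outcomes by the group × time interaction in a mixed-effects model. For the binary outcomes at Visit 10 it says: "The two-tailed Chi-squared test will be used to assess the significance of any observed differences in the proportion of responders and remitters" between groups.

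Section 1.1 gives background for TES and TMS: "response and remission rates for these modalities remain in the range of 33%–45% and 16%–22" per cent. The same sentence goes on to individual studies with much higher remission: 54% for tACS and 57%–86% for an accelerated theta-burst TMS protocol.

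**The concern.** The adequacy sentence is unrestricted, and response and remission are among the ways in which the plan tests for a therapeutic effect. Nothing in the sample-size section speaks to those two tests. The f = 0.25 calculation is for repeated continuous scores, and a two-sample comparison of proportions at one visit is a different test with different power.

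The gap matters because section 3.4 also says how a miss is to be read. If a non-significant p is taken as no difference with 90% confidence, a null responder or remitter result would count against tTIS even where the test had little chance of detecting a real effect.

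**Working it through.** **1. The plan's own figure.** Inputs from section 3.4: f = 0.25, two-sided α = 0.05, two groups, N = 30. For the group × time interaction, take λ = f²·N·m/(1 − ρ), with m measurements and correlation ρ. Neither m nor ρ is stated.

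With m = 4 and ρ = 0.5: λ = 0.0625 × 30 × 4 / 0.5 = 15, on 3 and 84 degrees of freedom, and power is 0.903. So 30 is reproduced under those choices. With ρ = 0.5 and N = 30, m = 3 (baseline, Visits 5 and 10) gives 0.84, and m = 5 (all HAM-D-17 visits in Table 2) gives 0.94. With 26 completers and m = 4 the power is 0.85. The 90% is attainable, but for this analysis only.

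**2. Numbers per arm for the binary tests.** 30 randomized 1:1 gives 15 per arm. After 15% dropout, 30 × 0.85 = 25.5, or about 13 per arm.

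**3. Method for the binary tests.** All 2×2 tables were enumerated with binomial probabilities. The probabilities of tables with active above sham and an uncorrected two-sided Pearson p ≤ 0.05 were summed. The statistic is χ² = 2n(ad − bc)² / [n²·s·(2n − s)], where n is the number per arm, ad − bc is the cross-product difference of the table and s is the total number of responders (or remitters).

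**4. Response.** The 50% is taken here as the active-arm rate. The sham rates are assumptions.

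| Active | Sham (assumed) | Power, 15/15 | Power, 13/13 |
|---|---|---|---|
| 50% | 5% | 0.87 | 0.80 |
| 50% | 10% | 0.73 | 0.66 |
| 50% | 20% | 0.42 | 0.41 |
| 50% | 30% | 0.19 | 0.22 |

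Power drops below one half once sham response exceeds about 17% (15/15) or 16% (13/13). If the 50% is instead the rate over both arms, 60% vs 40% gives 0.18 and 75% vs 25% gives 0.81 at 15 per arm. With a Yates correction or Fisher's exact test, power is lower: for 50% vs 20% at 15 per arm, 0.24 and 0.25.

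**5. Remission.** The best case for the test is no sham remitters, which can be checked by hand. With 15 per arm, 3 vs 0 gives χ² = 30 × 45² / (225 × 3 × 27) = 3.33, below 3.84. 4 vs 0 gives 30 × 60² / (225 × 4 × 26) = 4.62, above it. So at least 4 active remitters are needed. With 13 per arm the values are 3.39 and 4.73, so again 4 are needed.

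- At 22%, the top of the background range: P(X ≥ 4) = 0.43 for n = 15 and 0.32 for n = 13. Against 5% sham: 0.24 and 0.18.
- At 16%, the bottom of that range, with no sham remitters: 0.21 and 0.14.
- At 54%, the rate cited for tACS: 0.91 and 0.86 against 5% sham; 0.62 and 0.59 against 16% sham.

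**6. Precision.** For an assumed 50% vs 30% response with 13 per arm, the half-width of the 95% interval is 1.96 × √(0.25/13 + 0.21/13) = 1.96 × 0.188 = 0.37, or about ±37 percentage points.

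**The case against.** The best defence is that the plan never claims 90% power for the binary tests. That figure is tied to the mixed model, where it can be reproduced, and the adequacy sentence itself rests on earlier sample sizes. The section 2 hypothesis, that tTIS "will produce significantly greater improvement than sham stimulation", concerns scores on standardized scales. These are tested by the interaction term, so the chi-squared tests are an addition. The trial is a pilot whose stated purpose includes effect-size estimates for a definitive trial, and no go/no-go rule hangs on response or remission. All of this stands, and it is why the point is minor.

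A reader might go further and infer that, at the plan's own rates, the chi-squared tests would usually miss a real effect. The document does not support that as a general statement:

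- It gives no sham rate and names no arm for the 50%. For response, a miss becomes the more likely result only if sham response exceeds about 16–17%.
- The 16%–22% remission range is background on other modalities, not an assumption for this trial, and the same sentence cites 54% and more. At 54% the test can have good power.
- Low power in a secondary binary test does not refute the 90% stated for the mixed model.

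What the defence does not remove is the unrestricted wording of the adequacy sentence, together with the reading of p ≥ 0.051 as no difference.

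**Conclusion.** The point holds as a limit on what section 3.4 can claim. Its adequacy and 90% statements have support only for the mixed-model analysis, and only with unstated values such as m = 4 and ρ = 0.5. For response at 50% on active, power runs from 0.87 (0.80) down to 0.19 (0.22) as the assumed sham rate goes from 5% to 30%. For remission at 16%–22% it cannot exceed 0.43 (0.32), whatever the sham rate. At 54% remission it is 0.62 (0.59) or better for sham rates up to 16%.

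The document does not settle which of these applies, so a non-significant responder or remitter test cannot be taken as evidence of no difference. The calculation assumes the uncorrected chi-squared test, equal arms and analysis of either all 30 participants or about 26 completers. Severity is minor: these are secondary outcomes and the primary imaging outcomes are unaffected.

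**What to change.** In section 3.4:

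- limit the adequacy and 90% power statements to the mixed-model analysis;
- say that the effect on response and remission will be estimated, with an expected 95% interval of about ±37 percentage points for a response difference (assumed 50% vs 30%, 13 per arm);
- remove the reading of p ≥ 0.051 as no difference for these outcomes.

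In section 3.12.2, report response and remission as risk differences with 95% confidence intervals, and keep the chi-squared p-value as descriptive only.

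Section 2 needs no change, because its hypothesis concerns continuous scores. The cost is wording in two sections, with no added participants, visits or data. The stated claim becomes more modest and fits the pilot's aim of supplying effect-size estimates.

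### Section 3.4 reads p ≥ 0.051 as showing no difference with 90% confidence and defines power as confidence that an effect is true; neither is correct

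*Protocol article*

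**What the plan says.** The second paragraph of section 3.4 of the protocol article makes four statements about how results will be read.

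- 90% power is glossed as "being 90% confident that the effect is true and that it is not a type I/II error".
- On the interval, "the top end of the two-sided 95% confidence intervals will be the maximum confidence of having a true difference" between the arms.
- If there is no difference between the arms, p ≥ "0.051 will indicate no difference with a 90% confidence".
- If there is a difference, p ≤ "0.05 will indicate the difference with a 90% confidence".

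The same paragraph gives the sample size basis: an effect size of f = "0.25 for the mixed-model analysis of variance", for which "30 patients (15 per group) are required to have a 90% power". It adds: "We anticipate having a 15% dropout rate in the randomized phase of the study". Section 3.3 has participants "randomized into two parallel arms (active tTIS vs. sham) in a 1:1 fashion".

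The section gives no equivalence margin and no category for an inconclusive result. Nothing elsewhere in the article withdraws the four statements. The first paragraph of section 3.4 says the pilot is meant to supply effect size estimates and estimates of variability for a definitive trial.

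**The concern.** Power is a property of the test under a stated alternative: the chance that p falls at or below 0.05 if the specified effect is real. It is not the probability that a conclusion, in either direction, is right. A p-value above the threshold does not show equality; with 30 patients it is compatible with no effect and with a large one. The upper limit of a confidence interval is a value of the treatment difference, not a level of confidence.

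If the reading in section 3.4 were followed, inconclusive results would be written up as findings of no effect. That conflicts with the pilot's own purpose of estimating effect size, because an estimate with a wide interval is still informative for planning and a statement of no difference discards it.

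**Working it through.** **Inputs from the article.** 15 per arm, 1:1, f = 0.25, stated power 90%, 15% dropout (section 3.4; allocation in section 3.3). Two-sided α = 0.05, from the 95% interval and the p ≤ 0.05 threshold. The clinical test is the treatment group × time interaction in a mixed model (section 3.12.2). MRI is measured twice (section 3.10) and the HAM-D-17 five times (Table 2).

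**Not given in section 3.4.** The number of measurements m behind the sample size, and the correlation ρ between them. Both are varied below as assumptions.

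**1. The stated sample size.** For a within–between interaction with two groups, λ = f²·N·m/(1 − ρ), with m − 1 and (N − 2)(m − 1) degrees of freedom. With m = 4 and ρ = 0.5, λ = 0.0625 × 30 × 4/0.5 = 15.0 and power is 90.3%. With m = 3 and ρ = 0.6, power is 91.5%. So 30 patients for 90% power can be reproduced, but only for particular unstated choices.

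**2. The 90% attached to p ≥ 0.051.** If there is no true difference, p is uniform, so P(p ≥ 0.051) = 1 − 0.051 = 94.9% at any sample size. The 90% is neither this probability nor a consequence of 90% power.

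The probability of no difference given p > 0.05 needs a prior. With an assumed 50:50 prior it is 0.95/(0.95 + 1 − power). At 90% power this is 0.95/1.05 = 90%; at 26% power it is 0.95/1.69 = 56%. A figure near 90% therefore appears only under an assumed prior together with true power of 90%.

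**3. What p = 0.051 looks like for one between-arm contrast, 15 per arm.**

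- Standard error in SD units: √(2/15) = 0.365.
- Observed difference at p = 0.051: 2.039 × 0.365 = 0.74 SD.
- 95% half-width: 2.048 × 0.365 = 0.75 SD.
- 95% CI: just below 0 to 1.49 SD.
- At p = 1 (observed difference zero): −0.75 to +0.75 SD.

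**4. How often a single contrast is labelled no difference.** P(p ≥ 0.051) from the noncentral t distribution, with noncentrality d/√(2/n):

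| True difference | 15 per arm | 13 per arm (30 × 0.85 = 25.5) |
|---|---|---|
| 0.5 SD | 73% | 77% |
| 0.8 SD | 43% | 50% |
| 1.0 SD | 24% | 31% |

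**5. The same question for the planned interaction.** 1 − power at f = 0.25, N = 30, with the formula in step 1:

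| Measures m | ρ = 0.5 | ρ = 0.3 |
|---|---|---|
| 2 | 25% | 39% |
| 3 | 16% | 31% |
| 4 | 10% | 23% |
| 5 | 6% | 17% |

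Steps 4 and 5 differ because f = 0.25 does not mean the same thing in the two tests. At one time point it is d = 0.5. In the interaction with m = 2 and ρ = 0.5, λ = 7.5, which equals d²·15/2 at d = 1.0, so it corresponds to a between-arm difference in change of 1.0 SD. Smaller interaction effects would be missed more often than step 5 shows.

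**The case against.** **The sentence is conditional.** It begins by supposing that there is, or is not, a difference, so it can be read as a garbled account of operating characteristics. On that reading the half about p ≤ 0.05 is close to the ordinary definition of 90% power. This stands in part. But the other half should then say about 95%, and a reader of a p-value does not know which condition holds, so wording that p will indicate no difference can only be used from p to conclusion.

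**It is only in the sample size section.** This is true. Sections 3.12.1 to 3.12.3 do not repeat it, and section 3.12.2 says only that significance of the interaction tests the null hypothesis. The error is one of stated interpretation; no analysis changes.

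**The high miss rates come from a different test.** This also stands. The 73% and 43% describe a single contrast at one time point, not the planned interaction.

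**A stronger reading is tempting:** that the decision to run the larger trial would rest on p ≥ 0.051, and that a useful effect would usually be declared absent. The article supports neither. It states no go/no-go rule. The nearest text, at the end of the Discussion, says that successful target engagement would warrant further work, and section 3.12.1 defines engagement on functional connectivity by pre- versus post-treatment paired tests, not by this between-arm reading. As for usually, the single-contrast miss rate is already below half at 0.8 SD, and for the interaction at f = 0.25 it is 6–39% over the assumptions shown.

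**Conclusion.** The point holds as a misstatement of interpretation in section 3.4 that should be corrected. The definition of power, the reading of the upper confidence limit, and the 90% confidence attached to both p-value outcomes are wrong as written. The 94.9% in step 2 needs no assumption.

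The interval widths rest on a single between-arm contrast with 15 evaluable patients per arm and equal variances; there, a result labelled no difference can carry an estimate of 0.74 SD and an upper limit of 1.49 SD. How often real effects would be mislabelled depends on the test, the number of measures and their correlation, so no single rate can be quoted for the planned analysis.

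Correcting the text changes no endpoint, test or sample size. For that reason, and because no progression decision is tied to it, this is a should-fix rather than a must-fix.

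**What to change.** In section 3.4:

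- Delete the two sentences on 90% confidence and on the upper confidence limit, together with the gloss on power.
- Define power as the probability of p ≤ 0.05 if the specified effect is true.
- State that between-arm differences will be reported with 95% CIs, and that p > 0.05 is inconclusive and not evidence of no difference. This also closes the small gap between 0.05 and 0.051, which neither statement now covers.

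This costs wording only. A pre-set smallest difference of interest or formal progression criteria would be new design content; the correction does not require them, and they may belong in the full protocol or the analysis plan, which are not shown.
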